#### Secondary outcomes

Other data we collect as secondary outcomes include effect (negative) on mother-baby interaction [25, 26], breastfeeding practices, delivery that require assisted vaginal birth and/ or Caesarean section, adverse effects of mother and infant, admission to special care baby unit or neonatal intensive care unit, five-minute Apgar score, and infant outcomes at longer term follow-up.

### Demography and obstetrics data

Mothers’ demographic information is collected, such as maternal age, weight, height, socio-economic status, educational level, occupation, and marital status. Paternal age, occupation, and educational level are also noted. Other relevant obstetrical confounding factors of mothers on admission for labour – including parity, weeks of gestation, duration of labour prior to admission, degree of cervical dilation on admission and frequency of uterine contractions – are documented. During labour, information on any need for labour augmentation, foetal head position and status of amniotic fluid, are collected from medical records. Required infant data includes birth weight, gender, birth date, and body length. All the above information are recorded in the staff record form.

### Statistical methods

Baseline characteristics of the two groups are compared by an ANOVA test for continuous variables and χ [2]-test for categorical variables. The primary outcomes are differences in the mean change of VAS pre- and post-intervention between birth ball and other control methods first on the list, and differences in total scores of APS-POQ modified, c-LAS and SSQ between groups. Secondary measures are differences in c-PBQ score and mode of delivery (assisted vaginal and caesarean); differences in proportions of breastfeeding, adverse effects, admission to special care baby unit or neonatal intensive care unit, five-minute Apgar score less than seven; and differences in cost.

To control for potential cluster effect, (e.g., participants by certain midwives) we will use a linear mixed model where the midwife is treated as a random effect. The basic model is a random intercept model with compound symmetry as the covariance structure. The data fitness is explored using alternative models, e.g., using different covariance structures, will be compared by the restricted maximum likelihood.

Intention-to-treat analysis is adopted and performed by researchers masked to subjects’ group allocation. A two-sided *P* value of 0.05 or less is considered statistically significant. Objective measures and clinical outcomes are validated independently by two researchers. To minimise missing data, research officers ensure complete data collection prior to subjects’ hospital discharge and remind subjects that a follow-up assessment takes place at 6 to 8 weeks post-partum.

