### Randomisation and strata

This study adopts a two-arm (birth ball and control) randomised intervention-control trial design with block randomisation, as this is the most robust method of minimising selection bias and strengthening statistical power. We further enhance statistical power by using stratified randomisation according to potential confounders of parity (nulliparous or non-nulliparous) and type of labour onset (spontaneous or induced) – two strata give four possible combinations. Allocation is concealed by using sequentially numbered opaque sealed envelopes (in four separate sets) that contain group assignments determined by computer-generated random sequences. A research officer gives the sealed envelope to the health care worker who is intended to carry out the intervention. No intervention if subject is assigned to control.

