### Sample size

Data to estimate sample size is only available from two randomised trials [13, 14]. Both trials have high risks of bias that likely lead to an overestimated effect size (Cohen’s d 0.90–1.34) in labour pain relief by birth ball, measured by visual analogue scale (VAS).

Without existing rigorous research enabling more accurate estimation of effect size, we re-calculated sample size with a conservative Cohen’s d of 0.25 in pain relief measured by VAS, alpha 0.05 and a power of 0.8. This was calculated using software G*Power (version 3.1.9.2). In order to have an equal number of participants in intervention and control groups, participants of each stratified block are further amended as 64 in each stratum. This gives a sample size of 512.

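### Baseline balance is to be judged by significance tests, and the described outcome model names no role for the prognostic factors recorded on admission, which forgoes some precision

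*Protocol article*

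**What the plan says.** Three parts of the protocol article bear on this.

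- **Baseline comparison (Statistical methods).** "Baseline characteristics of the two groups are compared by an ANOVA test for continuous variables", and chi-square tests are used for categorical variables. No other use of baseline data is stated there, and no action is attached to a significant result.
- **Data recorded (Demography and obstetrics data).** Under the label "Other relevant obstetrical confounding factors of mothers on admission for labour" the protocol lists parity, weeks of gestation, prior duration of labour, and "degree of cervical dilation on admission and frequency of uterine contractions". It says that these are documented.
- **Outcome model (Statistical methods).** To deal with clustering, "we will use a linear mixed model where the midwife is treated as a random effect". Its starting form has one intercept per midwife and a compound-symmetric covariance, and other covariance structures are to be compared by restricted maximum likelihood. No fixed covariate is named.

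Parity and type of labour onset are handled in the design, as the two factors that define the four randomisation strata (Randomisation and strata). Baseline pain enters the first primary outcome by subtraction, because that outcome is defined as "differences in the mean change of VAS pre- and post-intervention between birth ball and other control methods".

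**The concern.** When allocation is random, any baseline difference between arms arises by chance, so a balance test examines a null hypothesis already known to be true. Its P value does not say whether an imbalance matters for the outcome. A non-significant difference in a strong predictor can matter, and a significant one in a weak predictor may not.

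The protocol labels several admission variables as confounders, prescribes balance tests on baseline data and names no covariate for the outcome model. That combination leaves open the choice to adjust, after seeing the data, for whatever proved significant.

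The second cost is precision. Three of the four primary outcomes (APS-POQ Modified, c-LAS and SSQ) have no baseline score in the protocol. State on admission is therefore a plausible source of prognostic information for them, it is already collected, and the described model does not use it.

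**Working it through.** **Inputs from the protocol.** Sample size section: "a conservative Cohen’s d of 0.25 in pain relief measured by VAS", alpha 0.05, power 0.8, equal arms, total 512. Statistical methods: two-sided testing. Assumed, because the protocol gives neither: the share of outcome variance explained by the admission covariates (R²) and their correlation with outcome.

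**1. The protocol's own figure.** n per arm = 2(1.96 + 0.842)²/0.25² = 251.2, so 252 per arm and 504 in total. The t-test version gives 253 per arm, 506 in total. Rounding to 64 per arm in each of four strata gives 64 × 4 × 2 = 512. The figure reproduces. With 256 per arm the t-test power is 0.806.

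**2. Effect of adjustment.** Adjustment reduces the residual SD by the factor √(1 − R²), so the standardised effect becomes 0.25/√(1 − R²). The equivalent extra number of women is 512/(1 − R²) − 512. Like the protocol's own calculation, this ignores clustering by midwife.

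| Assumed R² | Effect in residual SDs | Power, 256 per arm | Equivalent extra women |
|---|---|---|---|
| 0 | 0.250 | 0.806 | 0 |
| 0.05 | 0.256 | 0.825 | 27 |
| 0.10 | 0.264 | 0.845 | 57 |
| 0.15 | 0.271 | 0.865 | 90 |

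**3. How often balance tests flag something by luck.** Demography and obstetrics data lists 15 baseline items: 7 maternal, 3 paternal and 5 obstetric. If all were tested and were independent, the chance of at least one P < 0.05 would be 1 − 0.95¹⁵ = 0.54. Without parity it would be 1 − 0.95¹⁴ = 0.51. For the five obstetric items alone it would be 1 − 0.95⁵ = 0.23. Items such as education and occupation are likely to be correlated, and parity is balanced by design, so the true chance is somewhat lower.

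**4. What a balance test can miss.** The standardised baseline difference has SD √(2/256) = 0.088. One just short of significance is 1.96 × 0.088 = 0.173 SD. With an assumed correlation to outcome of 0.2 to 0.4, it moves the observed estimate by 0.035 to 0.069 SD, which is 14-28% of 0.25. That is an edge case. The average absolute difference is 0.798 × 0.088 = 0.07 SD, which moves the estimate by 0.014 to 0.028 SD, or 6-11% of 0.25. The unadjusted standard error already covers both.

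**The case against.** The strongest reply is that the article describes only a basic model and mainly its random part. It excludes no covariate, and a covariate list commonly sits in a statistical analysis plan, which is not shown here. Calling the admission variables confounding fits an intention to adjust at least as well as an intention not to. This stands. A reader might infer that no admission factor will enter the model, but the text supports only that none is named.

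A reader might also infer that chance imbalance leaves the primary estimates biased. It does not. Over repeated randomisation the unadjusted estimate is unbiased and its standard error allows for imbalance. Nor are all the listed factors used solely in balance tests, since parity is a stratification factor.

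Other parts of the reply stand as limits on size and remedy:

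- No R² or correlation is given, and 0.80 power is reached without adjustment. Eligibility restricts gestation to 37-42 weeks, and labour onset is already stratified, so the lower R² values are safer.
- Women may be admitted for induction, and for them prior labour duration may be zero or undefined.
- The Discussion expects ward staff to complete less of the research data than hoped, so added covariates could lose women unless missing values have a rule.
- The protocol attaches no action to a significant balance test, so data-driven adjustment is a possibility left open and not a stated plan. Such tests can also help to detect failed allocation.

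None of this rescues the balance tests as a guide to adjustment. They are prescribed in the text and do not depend on an unseen plan.

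**Conclusion.** The point holds as a matter of efficiency and pre-specification, not of validity. The protocol prescribes significance tests of baseline balance, which are no guide to adjustment in a randomised trial. The model that it describes names no role for the recorded admission factors other than the stratified parity. Neither the sample size of 512 nor the planned power of 0.80 is called into question.

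The gain forgone is modest: power of about 0.83 to 0.87 in place of about 0.81 at d = 0.25, worth 27 to 90 women, if the covariates explain 5-15% of outcome variance beyond what is already used. That range is an assumption. Even so, the gain is useful, because 512 exceeds the t-test requirement by only six women and the Sample size section states no allowance for loss. Removing the balance tests would by itself change no result. The benefit comes from fixing the covariates in advance.

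**What to change.** 1. Replace the ANOVA and chi-square baseline tests with a descriptive table by arm.
2. State that cervical dilation on admission and weeks of gestation are fixed covariates in the primary mixed models, chosen in advance and kept whatever the observed balance.
3. Add prior labour duration only if a value is defined for women admitted for induction.
4. Handle missing baseline covariates with a simple rule that keeps every randomised woman in the analysis, for example mean imputation with or without a missing indicator.
5. Do not adjust for items that arise during labour (augmentation, foetal head position, state of the amniotic fluid), since they may be affected by the intervention.

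If an existing analysis plan already does this, the article's wording need only be brought into line with it. The cost is small: the values are already on the staff record form, and two covariates use 2 of about 510 degrees of freedom. What is added is a little analysis work and the missing-value rule. The sample size does not change.

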### Inclusion & exclusion criteria

For safety reason, pregnant women who are admitted to the hospital for labour and vaginal birth will not be considered unless they meet all the inclusion criteria. 1) Chinese women able to provide informed consent; 2) singleton pregnancy in cephalic presentation planned for vaginal birth; 3) gestational age of 37 to 42 weeks admitted into a single room in labour unit, either in spontaneous active labour and the second stage not imminent, or for induction of labour; 4) uncomplicated past obstetrical and antenatal history enabling them to be under independent midwifery care.

The exclusion criteria are 1) Multiple pregnancy; 2) foetal mal-presentation contraindicating vaginal delivery; 3) complicated pregnancy requiring close monitoring and restricted mobilization; 4) Caesarean delivery planned for this pregnancy; 5) any of the contraindication to use birth ball listed for each hospital (slightly varies due to different setting).

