#### Primary outcomes

A simple and rapid visual analogue scale (VAS) of a 10-cm horizontal line, subdivided evenly with marks. Scores range from 0 (no pain) to 10 (extreme pain) are rounded to the nearest 0.1 cm, based on the women’s perceptions of pain at the time of assessment and during the peak of the last contraction at various time points: 1) on admission; 2) pre- and post-analgesia; 3) during labour, minimally every 2–4 h according to the phase of labour; 4) within 2 h of childbirth. This scale is the most widely used pain assessment scale in other birth ball studies [8–10, 13, 14]. Other primary outcomes are:

Satisfaction with pain relief
Modified satisfaction subscale from the American Pain Society – Patient Outcome Questionnaire (APS-POQ Modified) [20] is a 6-point scale (from ‘very dissatisfied’ to ‘very satisfied’) assesses women’s overall satisfaction of labour. The items regarding physicians are excluded.Additional questions on the willingness to use different analgesic methods in their next pregnancy and the most satisfied non-pharmacological method.
Sense of control in labour

A 29-item Chinese validated Labour Agentry Scale (c-LAS) [21, 22] is used. It has subjective statements such as ‘I felt confident’ and ‘I felt defeated’. Scores are given on a 7-point Likert scale (from ‘all the time’ to ‘almost never or never’).Satisfaction with childbirth experience

Six Simple Questions (SSQ) [23, 24] assesses women’s satisfaction with care during childbirth. Items are scored on a 6-point scale (from ‘strongly disagree’ to ‘strongly agree’), giving an overall score.

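### The primary VAS comparison uses a raw change score with no baseline VAS term in the described model, which loses precision that a covariate would recover

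*Protocol article*

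**What the plan says.** The Statistical methods section of the protocol article fixes the pain outcome as "differences in the mean change of VAS pre- and post-intervention", with the birth ball set against whichever control methods come first in a list. Of the model it says "we will use a linear mixed model where the midwife is treated as a random effect", and then "The basic model is a random intercept model with compound symmetry as the covariance structure". Alternative covariance structures are to be compared by restricted maximum likelihood. No fixed covariate is named and none is excluded. The one stated use of baseline data is to compare the two groups on it, by ANOVA or chi-square test.

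Baseline information is nevertheless collected. The Primary outcomes section has VAS recorded "at various time points: 1) on admission; 2) pre- and post-analgesia; 3) during labour, minimally every 2–4 h according to the phase of labour", and again shortly after the birth. None of these readings is labelled as the pre-intervention or post-intervention value. The Demography and obstetrics data section records "degree of cervical dilation on admission and frequency of uterine contractions" and treats these as confounding factors, but the analysis section gives them no role.

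The Sample size section uses Cohen's d = 0.25, alpha 0.05 and power 0.8 to reach 512 women. It does not say whether d is in units of the change-score SD or of the SD of a single VAS reading.

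**The concern.** A raw change score fixes the coefficient of the baseline reading at 1. Covariate adjustment estimates that coefficient. In large samples the estimated slope never gives a larger variance, and it gives a smaller one unless the true slope happens to be 1. When the pre/post correlation is below 0.5 (with equal SDs), the change score is noisier even than the follow-up value alone.

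A slope of 1 is unlikely here. Eligible women are "either in spontaneous active labour and the second stage not imminent, or for induction of labour", so starting pain may vary widely. On a scale bounded at 0 and 10, a high start leaves little room for a rise and a low start little room for a fall.

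What is at stake is precision. The standard error of the main pain comparison is larger than it needs to be and, on one reading of d, power falls below the planned 80%. A linked difficulty is that the starting point of the change is undefined for a control woman. If her reading is the one before whichever pain relief method she uses first, it may come after allocation and would not be a true baseline.

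**Working it through.** **Inputs from the article.** d = 0.25, alpha 0.05, power 0.8 and N = 512 (Sample size); two-sided testing (Statistical methods); two equal arms and four strata (Randomisation and strata; Sample size).

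**Assumptions.** The pre/post correlation rho and equal SDs s before and after are assumed, because the article gives no VAS SD and no correlation. Power is from a two-sample t-test and ignores clustering by midwife.

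**Step 1: the plan's own figure.** A two-sided t-test at d = 0.25 with 80% power needs 253 per arm, or 506 in total (504 by the normal approximation). Spread over 2 arms × 4 strata, 506/8 = 63.25, rounded up to 64, and 64 × 8 = 512. The figure reproduces. Power at 256 per arm is 80.6%.

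**Step 2: variances per woman.**
- Change score: 2s²(1 − rho)
- Baseline-adjusted: s²(1 − rho²)
- Ratio, adjusted to change: (1 + rho)/2, so the saving is (1 − rho)/2

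Without equal SDs the difference between the two variances is s_pre² × (1 − slope)², which is zero only when the slope is 1.

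Saving by assumed rho: 0.1 gives 45%, 0.3 gives 35%, 0.5 gives 25%, 0.7 gives 15% and 0.9 gives 5%.

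**Step 3: power at 256 per arm, if d = 0.25 is on the change-score SD.** The effective d after adjustment is 0.25/√((1 + rho)/2).

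| rho | ratio | power, change | power, adjusted | total N for 80%, adjusted |
|---|---|---|---|---|
| 0.3 | 0.65 | 80.6% | 93.8% | 330 |
| 0.5 | 0.75 | 80.6% | 90.3% | 380 |
| 0.7 | 0.85 | 80.6% | 86.5% | 430 |

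**Step 4: power at 256 per arm, if d = 0.25 is on the raw VAS SD.** The effective d is 0.25/√(2(1 − rho)) for the change score and 0.25/√(1 − rho²) after adjustment.

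| rho | power, change | power, adjusted |
|---|---|---|
| 0.3 | 66.5% | 84.1% |
| 0.5 | 80.6% | 90.3% |
| 0.7 | 95.4% | 97.7% |

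At rho 0.5 the change-score SD equals s, so the two readings of d coincide. Below 0.5, on the raw-SD reading, the unadjusted analysis drops under 80.6%.

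**Step 5: which reading is the covariate.** Steps 2 to 4 hold only if the covariate is the same reading that is subtracted to form the change. Suppose instead that follow-up VAS is adjusted for a different reading, the admission VAS. The variance ratio to the change score is then (1 − rho_adm²)/(2(1 − rho_pre)). With d on the change-score SD and assumed correlations:
- rho_pre 0.7, rho_adm 0.2: 0.96/0.60 = 1.60, power 60.7%
- rho_pre 0.6, rho_adm 0.3: 0.91/0.80 = 1.14, power 75.4%
- rho_pre 0.5, rho_adm 0.3: 0.91/1.00 = 0.91, power 84.1%

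Replacing the pre-intervention reading by a weakly correlated admission reading can therefore lose power.

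**The case against.** The strongest reply is that the article lists no fixed effects at all, not even arm or stratum, and that covariate lists commonly belong in an analysis plan, which is not shown. A change-score outcome does not preclude adjustment: regressing the change on arm and its own baseline gives the same arm effect as regressing the follow-up value on them. That stands in part. A reader might infer that the trial has ruled out baseline adjustment, and the article does not say so. It does, however, fix the comparison as a difference in mean change and describes its model without a baseline term, so a better use of data already collected is a fair point against the method as stated.

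The second reply is that nothing is invalid. The sample size reproduces, the bounded scale acts on both arms alike, and onset of labour is a stratification factor, so that source of spread is balanced by design. This also stands. A reader might infer that the change score biases the result. It does not if the starting reading precedes allocation or cannot be affected by it. The article does not settle when that reading is taken, and this is a reason to define it rather than evidence of bias.

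The third reply is that adjusting for the admission VAS is not automatically a gain, because the article never equates that reading with the pre-intervention one. Step 5 of the working bears this out, and the fix allows for it.

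**Conclusion.** The point holds as one of lost efficiency. The stated comparison is less precise than baseline adjustment unless the slope of follow-up on baseline is 1.

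The size depends on a correlation that the article does not give. A reader might quote a 15% to 35% loss as a property of this trial, but that range is only the result of assuming rho between 0.7 and 0.3 with equal SDs. Nor can the power gain be stated without a condition, because the article does not say which SD underlies d = 0.25. On the change-score SD the planned power is met without adjustment, and adjustment adds about 6 to 13 percentage points for rho 0.7 to 0.3. On the raw VAS SD the plan falls short of 80% when rho is clearly below 0.5, and adjustment restores it (84.1% at rho 0.3).

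The change is worth making because it uses data already collected and fits within the planned model.

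**What to change.** Keep the linear mixed model with midwife as a random effect and, before the analysts see allocation, specify the following:

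1. Name one baseline VAS reading, defined identically in both arms, that allocation cannot affect. Name the follow-up reading as well.
2. Enter that same baseline reading, the one used to form the change, as a fixed covariate.
3. Report the adjusted mean difference between randomised arms with its 95% CI as the primary pain result.
4. If the pre-intervention and admission readings differ, admission VAS and cervical dilation on admission may be added as further covariates. Admission VAS should not replace the pre-intervention reading where allocation cannot have affected the latter.
5. State whether d = 0.25 refers to the change-score SD or the raw VAS SD, and present any expected gain as (1 − rho)/2 with rho declared as an assumption.

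The cost is a few lines in the analysis plan. If the chosen reading is one of those already scheduled, no new data are needed. The sample size need not change for this.

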## Discussion

This study draws data from five different sites across Hong Kong, which will increase the generalizability of results and enable easier systematic adoption of the intervention in other non-trial units. With the large sample size, single-blinded and stratified randomisation design, the results we have will provide reliable data. We are using stratified randomisation according to potential confounders of parity (nulliparous or non-nulliparous) and type of labour onset (spontaneous or induced) – two strata give four possible combinations.

Taking ethical concerns into consideration, we are not forbidding women in the control group to use the birth ball if they request them, and vice-versa; we will not forcefully limit their other pain relief options. All the subjects from control group will remain in the control arm in the intention-to-treat analysis. This is regarded as a major limitation of the study that is not likely to be solved. Furthermore, since we aim to examine the effectiveness of the birth ball intervention as a whole in real clinical settings, these possible confounders are not intentionally separated out, as they are integral parts of birth ball application and implementation. Different hospitals have different cultures and settings, and hence this can lead to deviation in practice and therefore bias. To standardise the research protocol and administering of the intervention, meetings and training are given to the midwives at all study sites before and periodically during recruitment. There will be subgroup analysis in each hospital.

Other limitations of this study include the concomitant use of other non-pharmacological pain relief methods during labour. It is common for pregnant women to use several analgesic methods at the same time. Although the time and method of all the analgesic methods are noted, the outcome effects of using a birth ball would become difficult to measure. Besides, in a busy antenatal and labour ward, the completion of research data by midwives and staff would be less than expected. Our researchers follow-up each participant and ensure all the relevant information from the medical record is reviewed. Although it would be impossible to blind the midwives or physiotherapists who teach birth ball, all the researchers will not be disclosed the case or control status of participants in the ward and during data analysis.

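### Stratification by parity and labour onset is justified as a gain in power, but the stated mixed model does not name these factors; fitted as written, it would forgo most of that gain

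*Protocol article*

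**What the plan says.** Under "Randomisation and strata" the protocol article gives its reason for stratifying: "We further enhance statistical power by using stratified randomisation according to potential confounders of parity (nulliparous or non-nulliparous) and type of labour onset". It adds that "two strata give four possible combinations", with the allocation envelopes held "in four separate sets". Hospital is not described as a stratification factor.

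Under "Statistical methods" the analysis is described as follows: "we will use a linear mixed model where the midwife is treated as a random effect". The basic model is a random-intercept model with compound symmetry. Alternatives are to be compared by restricted maximum likelihood, and the only example given is a different covariance structure. Neither parity nor labour onset is named. The section lists no fixed effects at all, not even treatment arm.

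"Sample size" uses d = 0.25, alpha 0.05 and power 0.8 to reach 512 women and takes no credit for stratification. Hospital enters the analysis only as a planned subgroup analysis, mentioned in the Discussion.

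**The concern.** Stratified allocation balances the strata between arms, so differences between strata drop out of the treatment comparison and the estimate becomes more precise. A model without stratum terms does not see this. It leaves the between-stratum variance in the residual and reports a standard error that is larger than the true one. Confidence intervals are then too wide and the test rejects less often than 5% under the null hypothesis.

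The article therefore claims a power benefit in one section and, in another, describes a model that names nothing by which most of that benefit would be realised. The description goes as far as the random effect, the covariance structure and the estimation criterion, so the missing factors stand out. What is at stake is precision, not validity.

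**Working it through.** **Inputs.** From the article: d = 0.25, two-sided alpha 0.05, power 0.8, equal arms, four strata, total 512. Assumed, because the article gives no figure: R², the share of outcome variance explained by the four strata, taken from 0 to 0.20. For simplicity the formulas leave out midwife variance and take the arms as exactly balanced within strata.

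**The plan's own figure.** A two-sample t-test at d = 0.25 needs 253 per arm, or 506 in total. That is 253/4 = 63.25 per stratum and arm, rounded up to 64, and 64 × 4 × 2 = 512. The stated size is reproduced. Power at 256 per arm is 0.806 by the t distribution and 0.807 by the normal approximation used below.

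**Formulas.** In units of the total standard deviation:

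- SE reported without strata: s = sqrt(2/256) = 0.0884, so d/s = 2.828.
- True SE under stratified allocation: s × sqrt(1−R²).
- Ratio of reported to true SE: 1/sqrt(1−R²).
- True size without strata: 2 × Φ(−1.96/sqrt(1−R²)).
- Power without strata: Φ((2.828 − 1.96)/sqrt(1−R²)).
- Power with strata: Φ(2.828/sqrt(1−R²) − 1.96).

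| Assumed R² | Reported/true SE | True size, no strata in model | Power, no strata in model | Power, strata in model |
|---|---|---|---|---|
| 0 | 1.000 | 0.050 | 0.807 | 0.807 |
| 0.02 | 1.010 | 0.048 | 0.810 | 0.815 |
| 0.05 | 1.026 | 0.044 | 0.814 | 0.827 |
| 0.10 | 1.054 | 0.039 | 0.820 | 0.847 |
| 0.20 | 1.118 | 0.028 | 0.834 | 0.885 |

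**How much of the gain is forgone.** At R² = 0.10 the available gain is 0.8465 − 0.8074 = 0.0391. The part missed is 0.8465 − 0.8200 = 0.0265, or 68%. At R² = 0.20 it is 0.0512/0.0780, or 66%. About a third is kept without adjustment, because the estimate itself is more precise whatever SE is reported.

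**Simulation check** (6,000 runs per scenario, 64 women per stratum and arm, linear model without midwife effects). At R² = 0.20 the unadjusted test had size 0.028 and power 0.835; the adjusted test had 0.054 and 0.887. At R² = 0.10 the figures were 0.037 and 0.819 against 0.048 and 0.847. These agree with the formulas. At R² = 0.05 the simulated sizes were 0.049 and 0.055. The Monte Carlo standard error is about sqrt(0.05 × 0.95/6000) = 0.003, so that run cannot separate 0.044 from 0.050.

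**Hospital.** Reported SEs were compared between a model with a midwife intercept only and one that also allows for hospital. The comparison assumed five hospitals, 10 to 380 midwives each working in one hospital, and hospital variance shares of 0.02 to 0.10. Without hospital the reported SE was larger by less than 0.1% up to about 4%.

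**The case against.** The strongest reply is that the article is silent on the strata and does not exclude them. It lists no fixed effects, calls the model basic, foresees alternatives, and is a condensed account whose covariate list may stand in an analysis plan that is not shown. This stands as far as it goes: a reader might infer that the trial will leave the strata out, and the document does not say so. What remains is that it claims a benefit from stratifying and describes the model in some detail without the terms on which most of that benefit depends.

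The second reply is that the effect may be small. R² is assumed. For the change in VAS, stable differences between strata may partly cancel, and at R² near 0 nothing changes. This also stands. It applies less to the other three primary outcomes, which are total scores and not changes.

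A reader might also bring hospital into the point, because the Discussion warns that "Different hospitals have different cultures and settings, and hence this can lead to deviation in practice and therefore bias" and eligibility refers to any "contraindication to use birth ball listed for each hospital". The documents do not support this extension. Hospital is not described as a stratification factor, so omitting it cannot forfeit a stratification gain. Nor does it make the test conservative: chance imbalance in a factor that was not balanced by allocation is real sampling variation, and the reported SE properly includes it. The bias mentioned in the Discussion concerns deviation in practice, which a hospital term would not remove.

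The count of 42–76 trained staff does not show that midwife is a poor stand-in for hospital. The text does not make clear whether it is per hospital or in total, it includes physiotherapists, and staff without the certificate may also teach.

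**Conclusion.** The point holds in limited form. The article justifies stratification partly by power, and the model it describes does not name parity or labour onset. If that model were fitted as written, the SE would be 0–12% too large and the true size 0.050–0.028 over an assumed R² of 0 to 0.20. Power at the design effect would be 0.807–0.834 instead of 0.807–0.885.

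It would be wrong to conclude that the whole gain is lost, since about a third is kept. It would also be wrong to conclude that the trial is underpowered by this omission: 512 women give 80% power at d = 0.25 in the plan's own calculation, without any help from the strata. The treatment estimate is not biased and the type I error is not inflated. The consequence is a conservative test and some lost efficiency. Its size rests on R², which the article does not give, and on the simplifications stated in the working.

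**What to change.** In "Statistical methods", state that the primary mixed models include parity and labour onset (the four randomisation strata, that is, both factors and their interaction) as fixed effects alongside treatment arm, with midwife kept as a random effect. Both variables are known at randomisation, because they determine which envelope set is used. The cost is one sentence and about three degrees of freedom out of 512 women. If the analysis plan already contains these terms, the article need only say so. A hospital fixed effect is at most an optional addition, with a small effect on precision.
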